#### **4.4.4.3 Qualitative Interviews**

Participants may also be invited to partake in an interview to provide feedback after completion of the programme, to aid in service/intervention improvement in future. These interviews will take place in person or utilising UCC MS Teams. These interviews may be recorded, only with the participants consent, to allow for accurate transcription and documentation of the interview. Recordings will be stored on secure UCC internal servers only and deleted as soon as the recording has been transcribed and documented. These interviews will be optional and not mandatory.

#### **4.4.5 Duration of the Programme**

Patients will participate in the programme for a total of up to 12 months. They will complete surveys during the first 12 weeks of the study (Screening/Baseline and End of Treatment) and then at 6 months post intervention. Qualitative Interviews will take place within the 6 month post-intervention timeframe. In addition, participants will be invited to voluntary PPI engagement meetings quarterly after completion of the 12-week intervention programme for the duration of the study period (2 years).

#### **4.4.6 Electronic Patient Reported Outcomes (ePRO) Enrolment and Procedures**

Electronic Patient Reported Outcomes (ePROs) may be used to collect data directly from patients, specifically the quality of life questionnaires and any other self-reported, questionnaire-based tools, using a pseudoanonymised electronic data capture (EDC) system, CASTOR. This service is offered through the Clinical Research Facility-Cork (CRF-C), and meets national and international guidelines with respect to data privacy and protection standards. CRF-C staff will support the development of the ePRO survey template, study database construction and provide investigator training for downstream data collection, monitoring and analyses. Patient names will not be sent to the EDC database.

Patients will be emailed a link to the ePRO Symptom Survey at the specified timepoints (see schedule of activities) during the study period as required. Surveys can be accessed through any standard internet browser. Responses will be immediately uploaded to the study EDC database.

#### **4.4.7 Withdrawal/Discontinuation of Subjects**

All patients who initiate the study will be included in the overall analysis. All reasons for discontinuation of participation in the trial will be documented clearly in the trial record.

The reasons for discontinuation may include:

- a) At subject's own request.

Note: The reason for discontinuation from the study must be documented.

- b) Death.
- c) Intercurrent illness or condition that would, in the judgment of the principal investigator, affect assessment of clinical status to a significant degree.
- d) Evidence of disease recurrence during study.
- e) Study is terminated for any reason.
- f) Subject withdraws consent for follow-up.

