## The LIAM Mc Trial

This initial phase, 12-week programme of the first 6 men will be completed and analysed, including follow up and analysis, prior to commencement of the Expansion Phase from Q3 of year 1 onwards, see 3.2.1, Gantt Chart.

In the Expansion Phase, and for the remainder of the study period, parallel sampling groups will be used (i.e. after completion of the 6 participant Initial Phase). A new group of 6 participants will commence the programme every 6 weeks, in order to facilitate workload and resource management, see Figure 2. This will mean two groups are at two different timepoints in the programme at any given date. In total, 12 groups of 6 men are planned, including the initial phase group, with a total anticipated accrual of 72 participants over the two-year study period.

Data collection will occur at three designated timepoints; Baseline/Screening, and End of Treatment visit (after completing the intervention) and at 6 months post intervention. Completion of a process evaluation as part of the feasibility testing and secondary outcome measurement will also occur after all participants have completed the 12-week intervention programme.

**Subject recruitment:** June 2023-June 2025.

**Subject follow up period:** September M 2023-l December 2025 (12-18 months recruitment until 72 patients recruited + 6 months follow up for last patient enrolled)

Final data analysis: February 2026-

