### 4.3.3 End of Programme/Treatment Visit

At the end of programme/end of treatment visit, follow up questionnaires, burden of disease, nutritional, exercise and quality of life assessments will take place. This can be completed in the

final week of the intervention or within 14 days of programme completion. Full details and further information on the questionnaires, evaluations and processes are contained in the relevant sections below.

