### **Data related to patient comorbidities, medication, and clinician record of actions/follow-up at survivorship and symptom management encounters:**

Data relating to resource utilisation will be collected on an ongoing basis for the study group. Data relating to survivorship services that were provided by CUH or UCC and used during the study period will be recorded. Data on service utilisation (outside of CUH) will be collected throughout the study period by the information provided from the patient through the study patient's reports at each session and the 6-month follow up; this will include the services used, frequency of use, duration of each service and the personnel responsible for providing the service. This information will be collected by the Research Nurse.

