#### **4.4.9 Follow up**

Follow up for routine medical oncology care and surveillance will take place as normal, through the medical oncology clinics, see Figure 1. Flowchart. Study specific follow up will take place 6 months after completion of the 12-week intervention programme.

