### Abbreviations:

X – Scheduled Activity

A – Available on request

EoT – End of Treatment (**Note:** EoT assessments to be carried out during week 12 of intervention programme or within 2 weeks of completing the programme).

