### 6.1 Sample size justification

Parallel Sampling Groups will be used from Q3 of Year 1 on (after completion of the 6 participant Initial Phase). A new group of 6 participants will commence the programme every 6 weeks, in order to facilitate workload and resource management (see Figure 2, Section 3.2.1). This will mean two groups are at two different timepoints in the programme at any given date. 12 groups of 6 men each are planned in total, including the pilot phase group, with a total anticipated accrual of 72 participants over two years.

Given that the main objectives of this study are to evaluate the *feasibility* of introducing a men's malignancy survivorship programme, we have not calculated the sample size that would be required to reliably estimate the effect of the programme on patient outcomes. This follows from established best practices in pilot and feasibility studies [19] for which there is usually too much uncertainty in the various factors that are needed to make a sample size calculation robust (e.g. effect sizes of interest, outcome variability, etc.). Our sample size justification is instead based on trying to recruit the largest possible sample given existing financial and pragmatic constraints. This will allow us to maximize our ability to identify barriers to implementation, as well as the information that will be required to properly design any subsequent trials of the programme's efficacy (e.g. robust estimation of estimator variability, even for binary outcomes [20]). At the same time, the potential costs of over-recruitment are largely absent for this study. Most importantly, there are no excess risks to patients receiving the intervention, and all patients are guaranteed access to the current standard of care. Further, most of the financial costs of the study are fixed, regardless of the actual number of patients recruited into the study.

Given that the goal of a feasibility study is to identify problems that would impede the conduct of a larger, efficacy study, we have set the sample size at 60 based on advice from Viechtbauer et al. [21], which is aimed at being able to detect failures in study processes that would occur just 5% of the time (with 95% confidence). A sample size of 72 allows for sample attrition from men withdrawing, illness, or waning commitment as commented.

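### Section 4.4.7 counts every man who starts, but the protocol never says that a man who stops the programme early is still assessed, and its timing rules diverge for him

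*Protocol*

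**What the plan says.** Protocol section 4.4.7 sets the analysis population: "All patients who initiate the study will be included in the overall analysis". It then gives a single list of reasons for discontinuing trial participation. The list includes the man's own request, death, intercurrent illness and disease recurrence. Withdrawal of consent for follow-up is a further item in the same list, with no procedure attached.

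Several places date the later assessments from completing the programme:
- Section 3.2: "End of Treatment visit (after completing the intervention) and at 6 months post intervention".
- Section 4.3.3 places the EoT visit in the "final week of the intervention or within 14 days of programme completion".
- The note to the schedule in section 5.0: "EoT assessments to be carried out during week 12 of intervention programme or within 2 weeks of completing the programme".
- Section 4.4.9: "Study specific follow up will take place 6 months after completion of the 12-week intervention programme".

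Other places use the calendar. Section 4.3.2 has assessments at baseline, 12 weeks and 6 months. Section 4.4.3.1 (physiotherapy outcomes) and section 4.4.4.2 (quality of life) give week 12 with a window of 14 days either side. Section 4.4.4.1 puts the nutritional and anthropometric measures at week 12.

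Use of services outside Cork University Hospital (CUH) is gathered, under section 4.4.4, "through the study patient's reports at each session and the 6-month follow up". On expected loss, section 6.1 says: "A sample size of 72 allows for sample attrition from men withdrawing, illness, or waning commitment as commented".

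**The concern.** The promise to analyse everyone who starts needs a matching rule for collecting data on everyone who starts, and the protocol has none. Consider a man who becomes ill in week 5, stops attending, and is still willing to fill in questionnaires. Under the completion-dated sections he never reaches the event that sets his EoT and six-month dates. Under the calendar-dated sections he is due at week 12. No section says which applies to him, and the schedule has no early-stop visit.

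The loss is unlikely to be random, since illness and recurrence are themselves listed reasons for leaving. There is no control group, so the results on quality of life, fatigue, strength and body composition are plain changes from baseline. If men who are doing worse drop out of those changes, the programme looks better than it was. Section 2.1 intends these data to support offering the programme to all patients. An analysis plan cannot repair this afterwards, because it cannot recover measurements that were never taken.

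**Working it through.** **1. Is there a rule for a man who stops early?**

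| Protocol place | Anchor | What it gives a man who stops in week 5 |
|---|---|---|
| 3.2, 4.3.3, 5.0 note | completion (or the programme's last week) | no clear EoT date |
| 4.4.9 | 6 months after completion | no clear follow-up date |
| 4.3.2, 4.4.3.1, 4.4.4.1, 4.4.4.2 | calendar week 12 | an EoT date exists |
| 4.4.7 | none | reason for leaving is recorded |
| 4.4.7.1 | none | allows a replacement if he withdraws before the start or in the first 4 weeks |

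For a man who finishes on time the anchors agree. For a man who stops they do not, and even the calendar sections blur the matter: section 4.4.3.1 calls its week-12 point the end-of-programme visit, and section 4.4.4.2 counts its six-month point from the end of the intervention. Section 4.4.7.1 shows that the protocol recognises withdrawal from the intervention as a distinct event, but it deals only with replacement.

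**2. Which data are exposed?**
- In-person measures (bioimpedance, 8-repetition maximum, grip strength, 6-minute walk) need a visit.
- Questionnaires can be sent by the emailed link of section 4.4.6, at the time points of the schedule, whose EoT note refers to completion.
- Services provided by CUH or UCC are recorded (section 4.4.4), and CUH services are also taken from hospital records (section 4.4.10). Only services used outside CUH rest on the man's own report.

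**3. The plan's own figures.** Section 6.1 wants to detect a process failure of 5% probability with 95% confidence:

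n = ln(1 − 0.95) / ln(1 − 0.05) = 58.4, so 59. The stated 60 agrees to within one man.

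The rise from 60 to 72 leaves 12 men, and 12/72 = 16.7%. The protocol states no attrition rate, so this is only the loss that the two figures imply. The sample size itself is not affected by this point.

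**4. How large could the distortion be?** Let p be the share of starters without an EoT value, and g the amount by which leavers' mean change is worse than completers'. Then

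completers' mean − mean of all starters = p × g.

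Both p and g are assumptions. Taking g as 10 to 20 points on a 0 to 100 quality-of-life scale:

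| Lost before EoT | p | g = 10 | g = 20 |
|---|---|---|---|
| 7 of 72 | 9.7% | 1.0 | 1.9 |
| 12 of 72 | 16.7% | 1.7 | 3.3 |
| 22 of 72 | 30.6% | 3.1 | 6.1 |

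For example, 12/72 × 10 = 1.7 and 12/72 × 20 = 3.3. With g = 5 the middle row gives 0.8.

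**5. How much of that is avoidable?** If every leaver could still be assessed, all of it; if none could, nothing. Men who die or withdraw consent for follow-up stay missing under any rule, so the avoidable part lies between these ends and the documents do not say where.

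**The case against.** Stronger readings are tempting, and the documents do not support them.

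- *Every later assessment depends on completion.* Not so: four sections give calendar week 12. Each group also runs a fixed 12-week course, so completion could be read as a date that exists for every man in the group. This shows that the protocol may intend continued assessment. It does not show that it says so, and the two sets of sections still need reconciling.
- *The change results are restricted to completers.* No section says this. Men who miss sessions but stay enrolled still reach EoT, and a man who stopped could be reached by emailed link or phone. Reliance on completers is a likely consequence, not a stated rule.
- *Nothing but the reason for stopping is collected.* Section 6.2 counts enrolled men who complete assessments and who take part in all or fewer activities, and section 7.1 records adverse events potentially related to the intervention throughout the study. These cover men who stop.
- *Service use is no longer observed once a man leaves.* This fails for CUH and UCC services, which are recorded or taken from hospital records. For outside services it assumes that the six-month report is not obtained, which no section states.

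It is also fair to say that the main aim is feasibility and that the handling of missing values commonly belongs in an analysis plan. That stands for the analysis method. It does not answer whether the data are collected, which is a matter for the protocol. Finally, the sizes above depend on assumed gaps and an unstated loss rate, which also stands.

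**Conclusion.** The point holds as a gap in data collection. The protocol promises to include all men who start, treats illness and recurrence as leaving the trial, and does not say that a man who stops the programme is still assessed. Its completion-based and calendar-based anchors agree for completers and diverge for him. Followed as written, the before/after changes are likely to come mainly from completers and to look too favourable, and patient-reported use of services outside CUH may be incomplete.

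The size is unknown. The figure of about 1.7 to 3.3 points rests on three assumptions: 12 of 72 men lost, all of them before EoT, and leavers doing 10 to 20 points worse. Only part of it could be avoided. The feasibility counts and the sample size are untouched. This is a cheap improvement that should be made, not a flaw that undermines the study.

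**What to change.** In section 4.4.7, separate stopping the programme from withdrawing consent for data collection. For men who stop but have not withdrawn that consent:

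- keep the EoT assessments at calendar week 12, with the 14-day window either side already in sections 4.4.3.1 and 4.4.4.2;
- keep the six-month questionnaires and the report of outside service use at a fixed date counted from programme start. About week 38 (12 + 26) matches the date for men who complete on time;
- use the ePRO link (section 4.4.6) or the phone call (section 4.3.2) for men who cannot attend.

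Align sections 3.2, 4.3.3, 4.4.9 and the note to section 5.0 with this. Report the number of men contributing to each change result, split by completed or stopped.

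The cost is wording in these sections and a few extra contacts, for roughly 12 men if the implied loss occurs. Some in-person measures will still be missing for men who cannot attend. No rule on when a man should stop the programme needs to change.

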#### 4.4.7.1 Replacement of Subjects

Note: If a participant withdraws from the intervention within the first 4 weeks of the 12-week intervention programme or after consent but prior to the 12-week programme commencing, an alternative participant may enroll in the programme, provided they are willing to join at that point of the programme.

#### 4.4.8 Usability and Satisfaction

In order to gather information on usability and satisfaction with the intervention, the opinions of patients will be gathered using a modified five-item Usability and Satisfaction Survey [17,18]. The questions in this index are designed to assess different domains of usability related to the programme, including usefulness, ease of use and satisfaction with use, and were adapted from a previously developed computer usability and satisfaction questionnaire. The survey will also include some open-ended questions allowing participants to share their perspectives more freely.

As part of the process evaluation, all patients, some health care professionals and some of the broader team involved in the development and implementation of the programme will be invited to provide feedback after the completion of their involvement in the study (in person or remotely). Attendees will be asked about their experiences of the survivorship programme and associated processes, limitations, challenges and possible benefits and future possibilities concerning the intervention. A questionnaire with open ended questions will be provided based on the outcome of the rapid review.

Participants in the 12-week programme will also be invited to quarterly PPI engagement sessions to provide group feedback on the programme, and some participants may be invited to partake in the steering group as additional PPI members.

The interview will be audio-recorded with the consent of participants (both patients and HCPs), and will last approximately one hour. Transcribed audio will be analysed using qualitative content analysis. A priori it is anticipated that we will interview up to twenty patients, ten members of the MDT and ten broader team/stakeholders/service providers. A lesser number may be required if data saturation is attained earlier.

#### **4.4.9 Follow up**

Follow up for routine medical oncology care and surveillance will take place as normal, through the medical oncology clinics, see Figure 1. Flowchart. Study specific follow up will take place 6 months after completion of the 12-week intervention programme.

#### **4.4.10 Data extracted from patient hospital records**

Patient data including age, sex, cancer site, diagnosis, treatment, current medications will be extracted from the patient records exclusive of patient identifiers from The Orchid Centre database located in Cork University Hospital. All survivorship services that were provided by the CUH and used during the study period will be extracted from the patient records and from patient reports.

## 5.0 Schedule of Activities

**Schedule of Activities.** Assessments to be performed at the times stipulated in the table and as clinically required in the management of the patient.

| Timepoint                                   | Screening
(-6 weeks) | Week
1 | Week
2 | Week
3 | Week
4 | Week
5 | Week
6 | Week
7 | Week
8 | Week
9 | Week
10 | Week
11 | Week
12 | EoT | Follow-up
(6 Months) |
|---------------------------------------------|-------------------------|-----------|-----------|-----------|-----------|-----------|-----------|-----------|-----------|-----------|------------|------------|------------|-----|-------------------------|
| Phone call and patient information leaflet  | X                       |           |           |           |           |           |           |           |           |           |            |            |            |     |                         |
| Written informed consent                    | X                       |           |           |           |           |           |           |           |           |           |            |            |            |     |                         |
| Demographics                                | X                       |           |           |           |           |           |           |           |           |           |            |            |            |     |                         |
| Previous treatments for cancer              | X                       |           |           |           |           |           |           |           |           |           |            |            |            |     |                         |
| Medical and surgical history                | X                       |           |           |           |           |           |           |           |           |           |            |            |            |     |                         |
| Formal verification of eligibility criteria | X                       |           |           |           |           |           |           |           |           |           |            |            |            |     |                         |
| Vital signs, including weight               | X                       |           |           |           |           |           |           |           |           |           |            |            |            | X   |                         |
| Physical exam                               | X                       |           |           |           |           |           |           |           |           |           |            |            |            | X   |                         |
| ECOG performance status                     | X                       |           |           |           |           |           |           |           |           |           |            |            |            | X   |                         |
| Current medication List                     | X                       |           |           |           |           |           |           |           |           |           |            |            |            |     |                         |
| Baseline physical assessment                | X                       |           |           |           |           |           |           |           |           |           |            |            |            |     |                         |
| Body composition assessment     | X                       |           |           |           |           |           |           |           |           |           |            |            |            | X   |                         |

